## Abstract

**Highlights:**

**What are the study objectives and methodological features?**
This protocol establishes a standardised framework to assess self-reported home exercise adherence in adults undergoing rehabilitation for whiplash-associated disorders or non-surgical post-traumatic neck pain.It predefines the targeted population, eligibility criteria, timing of the Exercise Adherence Rating Scale (EARS) administration, core variables, and a structured statistical analysis plan.

**What are the potential methodological contributions?**
The protocol aims to support consistent and reproducible documentation of adherence within cervical trauma rehabilitation settings.It provides a methodological basis to help researchers and clinicians systematically document exercise exposure, facilitating clearer distinctions between treatment efficacy and adherence issues.

**Abstract:**

**Background/Objectives:** Whiplash-associated disorders (WADs) and non-surgical post-traumatic neck pain often require active rehabilitation, including prescribed home exercise, where poor adherence can limit treatment effectiveness. This protocol describes a standardised observational method to assess home exercise adherence using the Exercise Adherence Rating Scale (EARS). **Methods:** This prospective protocol outlines eligibility criteria, recruitment settings, core variables, and a structured EARS administration procedure four weeks post-prescription. The primary outcome is the six-item EARS adherence section score. A target sample of approximately 75 participants will be recruited to ensure at least 62 analyzable participants. **Outputs:** The protocol will generate descriptive data on adherence levels, questionnaire completion rates, and missing data to evaluate implementation feasibility. Planned analyses testing potential associations between adherence and clinical variables will be strictly exploratory and hypothesis-generating. **Conclusions:** This study operationalizes a standardised method for tracking self-reported adherence in cervical trauma rehabilitation, enhancing methodological transparency and reproducibility.

## 1. Introduction

Whiplash-associated disorders (WADs) occur after acceleration–deceleration mechanisms affecting the neck and may lead to neck pain, stiffness, restricted movement, headache, dizziness, upper-limb symptoms, and functional limitations [1,2]. The available epidemiological evidence indicates that WAD after traffic collisions affects a relevant proportion of the population and represents a considerable health, social, and economic burden [1,3]. Although many patients recover during the first months after injury, recovery is not uniform. A best-evidence synthesis from the Bone and Joint Decade Task Force reported that approximately 50% of people with WADs continue to report neck pain one year after injury [2]. Distinct clinical trajectories have also been described, including chronic-severe pain/disability and persistent post-traumatic stress symptoms [4].

Usual conservative care for WADs and non-surgical post-traumatic neck pain typically includes reassurance, education, advice to remain active, gradual return to usual activities, supervised physiotherapy when indicated, and therapeutic exercise delivered both in clinic and at home [5,6]. Current clinical practice guidelines recommend multimodal management combining education, self-management advice, exercise therapy, mobilisation or manual therapy, and functional progression according to the patient’s clinical profile [5,6]. Systematic reviews support the use of active interventions and exercise therapy, although the quality of evidence remains variable, and no single exercise approach has been consistently shown to be superior for all patients [7,8,9].

The effectiveness of exercise-based rehabilitation depends not only on what is prescribed, but also on the degree to which patients implement the prescribed programme. Treatment adherence is not passive obedience to clinical instructions, but an active process in which the patient’s behaviour corresponds with agreed recommendations from the healthcare professional [10,11]. In physiotherapy, adherence is multidimensional and may include attendance at treatment sessions, active participation during treatment, performance of home exercise, frequency and quality of execution, and avoidance of contraindicated activities [12].

Home exercise adherence is particularly challenging because the programme is performed outside the supervised clinical environment and depends on self-efficacy, motivation, social support, symptom behaviour, contextual barriers, and the feasibility of integrating exercise into daily life [13,14,15,16,17,18,19]. In cervical trauma rehabilitation, adherence assessment is especially relevant because symptoms may fluctuate over time, psychological factors may influence recovery, and home exercise is often used to promote self-management and progressive return to function. Without standardised adherence assessment, it is difficult to determine whether limited improvement reflects treatment ineffectiveness or insufficient exposure to the prescribed programme.

Measuring adherence to home exercise remains a methodological problem. Systematic reviews have shown marked heterogeneity in the methods used to assess adherence in home-based rehabilitation, with frequent reliance on diaries, self-reported questionnaires, and ad hoc measures [20,21,22]. This lack of standardisation limits comparability between studies and reduces the interpretability of exercise-based rehabilitation outcomes.

The Exercise Adherence Rating Scale (EARS) was developed to provide a brief, exercise-specific, patient-reported measure of adherence to prescribed home exercise [23]. The main adherence section consists of six items scored on a Likert-type scale, with a total score ranging from 0 to 24, where higher scores indicate greater adherence [23,24]. The original development study reported a one-factor structure explaining 71% of the variance in exercise adherence and acceptable psychometric properties [23]. Since then, the EARS has been adapted and evaluated in several languages and musculoskeletal populations, including Brazilian Portuguese, Nepali, Japanese, Swedish, Mexican Spanish and Persian versions [24,25,26,27,28,29].

To the authors’ knowledge, no previous protocol has specifically standardised the use of the EARS to assess adherence to prescribed home exercise in adults undergoing rehabilitation after WAD or non-surgical post-traumatic neck pain. This does not imply that the EARS has been psychometrically validated for this population. Rather, it identifies the need for a reproducible implementation protocol that can support consistent adherence assessment and inform future validation studies.

The primary research question of this protocol is as follows: What is the level of self-reported adherence to prescribed home exercise, measured with the EARS, in adults undergoing rehabilitation after WAD or non-surgical post-traumatic neck pain? Secondary research questions are as follows: Is EARS administration feasible in this clinical context, and are EARS scores associated with predefined clinical or rehabilitation-related variables such as pain intensity, time since injury, number of supervised sessions, and characteristics of the prescribed home exercise programme? The exploratory hypothesis is that lower adherence may be associated with higher pain intensity, longer time since injury, lower supervised contact, and higher prescribed home exercise burden. Publishing this study protocol prior to data acquisition promotes scientific transparency and reproducibility. By pre-registering the study hypotheses, eligibility criteria, and primary endpoints, this framework mitigates publication bias and prevents selective outcome reporting. Furthermore, early dissemination allows independent investigators to evaluate or replicate the tracking infrastructure, contributing to the standardisation of exercise adherence metrics within cervical trauma rehabilitation before data collection begins.

## 2. Experimental Design

### 2.1. Study Design

This manuscript describes a prospective observational protocol for assessing self-reported adherence to prescribed home exercise. It does not propose an experimental intervention, randomisation, or allocation to treatment groups. The protocol is designed to standardise adherence assessment in patients receiving usual physiotherapy care after WAD or non-surgical post-traumatic neck pain.

The protocol does not aim to evaluate the therapeutic effectiveness of a specific physiotherapy intervention and does not aim to validate the EARS psychometrically in this population. Psychometric validation, including reliability, validity, responsiveness, and floor or ceiling effects, is considered a subsequent research step. The present protocol focuses on standardised implementation, feasibility of administration, and exploratory associations between EARS scores and predefined contextual variables.

### 2.2. Setting and Recruitment

Participants will be recruited from outpatient physiotherapy and rehabilitation clinics affiliated with the University of Seville or collaborating clinical centres. Recruitment will begin only after approval by the corresponding Ethics Committee and is expected to continue for approximately 12 months, or until the target sample size has been reached.

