#### 2.6.2. Mandatory Core Variables

The following secondary variables will be collected to contextualise adherence:Age and sex.Diagnostic category: WAD grade I-II or non-surgical post-traumatic neck pain.Time since injury and predefined time-since-injury category.Mechanism of injury.Pain intensity using a numerical rating scale or visual analogue scale (VAS).Number of supervised physiotherapy sessions completed before EARS administration.Home exercise programme characteristics: number of exercises, prescribed weekly frequency, estimated session duration, dose, progression instructions, and instructional format.EARS total score and item-level missingness.Self-perceived barriers to exercise.

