### 2.9. Sample-Size Rationale

The sample-size rationale is based on the precision of the descriptive estimate of the mean EARS score rather than on hypothesis testing. Assuming a conservative standard deviation of approximately 6 points for the EARS total score and a desired 95% confidence interval half-width of approximately 1.5 points, at least 62 analyzable participants would be required. To account for incomplete questionnaires, withdrawal, or loss to follow-up, the target recruitment sample will be approximately 75 participants. Exploratory association analyses will be interpreted cautiously and will not be considered confirmatory.

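### The 1.5-point precision figure assumes independent participants although recruitment is from several clinics, and neither clinic nor treating therapist is among the listed variables

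*Protocol article*

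**What the plan says.** Recruitment is from more than one site. Section 2.2: "Participants will be recruited from outpatient physiotherapy and rehabilitation clinics affiliated with the University of Seville or collaborating clinical centres". The number of clinics is not given.

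Precision is the only justification of the sample size. Section 2.9: "The sample-size rationale is based on the precision of the descriptive estimate of the mean EARS score rather than on hypothesis testing". Its inputs are "Assuming a conservative standard deviation of approximately 6 points for the EARS total score" and "a desired 95% confidence interval half-width of approximately 1.5 points", from which "at least 62 analyzable participants would be required". The uplift, "the target recruitment sample will be approximately 75 participants", is attributed to unusable questionnaires and attrition. Clustering is not mentioned.

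Section 2.6.2 introduces its mandatory list with "The following secondary variables will be collected to contextualise adherence". The list covers demographics, diagnosis, injury, pain, supervised sessions, programme characteristics, EARS data and barriers. It has no clinic or therapist. The optional list in Section 2.6.3 has neither, and Section 3.2 defines the clinical data sheet by these two lists. The programme record (Section 3.3) and the baseline dataset (Section 4.4) do not name them either.

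Section 4.9 plans a 95% confidence interval for the EARS total, bivariate tests and a linear regression with six candidate predictors. No clinic or therapist term appears in any of these.

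**The concern.** Patients treated in the same clinic or by the same therapist may have more similar adherence scores than patients from different clinics. Sections 2.5 and 4.5 make the treating clinician responsible for the content of the prescription, and supervised contact and teaching method may also follow local practice. If scores are correlated in this way, 62 patients carry less information about the mean than 62 independent patients, and an interval built on SD/√n is too narrow for inference beyond the participating clinics.

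The stake is the primary result. The study exists to estimate one mean with stated precision, and that precision rests on the independence assumption. The exploratory tests and regression make the same assumption. Because clinic is not in the planned dataset, the analyst could not tell from that file whether the assumption is reasonable.

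**Working it through.** **Inputs from the protocol article.** SD = 6, 95% confidence, half-width h = 1.5, 62 analysable and about 75 recruited (all Section 2.9); several clinics, number not stated (Section 2.2).

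**Inputs that are assumed.** Number of clinics K = 3, 5 or 10; ICC = 0.01, 0.05 or 0.10; equal clinic sizes m = 62/K. None of these is in the documents.

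**Step 1: reproduce the plan's figure.** n = (1.96 × 6 / 1.5)² = 61.46, rounded up to 62. The figure is reproduced exactly. At n = 62 the half-width is 1.96 × 6/√62 = 1.49. This is the formula with a design effect of 1.

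**Step 2: allow for clustering.** Design effect DE = 1 + (m − 1) × ICC; half-width = 1.49 × √DE; coverage of the uncorrected interval = 2Φ(1.96/√DE) − 1.

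Example with K = 5 and ICC = 0.05: m = 62/5 = 12.4; DE = 1 + 11.4 × 0.05 = 1.57; effective sample size = 62/1.57 = 39.5; half-width = 1.49 × √1.57 = 1.87; coverage = 2Φ(1.96/1.253) − 1 = 88.2%.

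| Clinics | ICC | DE | Half-width (points) | Coverage of uncorrected 95% CI |
|---|---|---|---|---|
| 3 | 0.01 | 1.20 | 1.63 | 92.7% |
| 3 | 0.05 | 1.98 | 2.10 | 83.6% |
| 3 | 0.10 | 2.97 | 2.57 | 74.5% |
| 5 | 0.01 | 1.11 | 1.58 | 93.7% |
| 5 | 0.05 | 1.57 | 1.87 | 88.2% |
| 5 | 0.10 | 2.14 | 2.18 | 82.0% |
| 10 | 0.01 | 1.05 | 1.53 | 94.4% |
| 10 | 0.05 | 1.26 | 1.68 | 91.9% |
| 10 | 0.10 | 1.52 | 1.84 | 88.8% |

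At ICC = 0 the half-width stays at 1.49.

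**Step 3: does the recruitment margin absorb it?** If all 75 recruits were analysable, a design effect of up to 75/61.46 = 1.22 could be absorbed. With 5 clinics that covers ICC 0.01 but not 0.05. The margin is meant for attrition, so it cannot be counted on for clustering as well.

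**Step 4: what a cluster-aware interval would look like.** The half-widths above use the normal quantile. With 5 clinics an interval on K − 1 = 4 degrees of freedom uses t = 2.776, so at ICC 0.05 the half-width is 2.776 × 6 × √(1.57/62) = 2.65 points.

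**The case against.** A reader might infer that the interval will be too narrow and that nothing can be done about it once the data are in. The documents support neither statement.

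- **Narrowness is conditional.** It needs a positive ICC and an inference beyond the participating clinics. No ICC or number of clinics is given. With 10 clinics and ICC 0.01 the half-width moves only from 1.49 to 1.53. If the participating clinics are treated as fixed, the loss is small or nil. Individualised prescribing (Section 2.5) points at least as much to variation between patients as between therapists. Therapist-level clusters would also be smaller: with an assumed 15 therapists at ICC 0.05, m = 62/15 = 4.1, DE is about 1.16 and the half-width about 1.61.
- **Recovery is possible.** Section 4.3 keeps the link between participant code and identity in separate storage. While it exists, clinic, and probably therapist, could be traced through clinical records.
- **The article is condensed.** A site identifier and the choice of standard error are often left to the full data sheet or the analysis plan, which are not shown. The association analyses are already labelled exploratory.

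The first two arguments stand and limit the claim. The third stands in part. Section 3.2 defines the data sheet by the two published lists, and Section 2.10 restricts collection to what the objective requires, so an undeclared clinic field has no stated basis. A later analysis plan can change a model but does not by itself add a field to the collection form. The fixed-clinic argument is also weakened by Sections 1 and 2.3, which frame the question and target population as adults in rehabilitation generally. Recovery through the identity link is possible but unplanned, and Section 4.8 puts only the participant code in the analysis file.

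**Conclusion.** The point holds in conditional form. The stated precision is correct under independence. Recruitment is multi-clinic, no part of the sample size or analysis allows for that, and the variables needed to examine it are not listed.

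Whether the effect is material cannot be settled from the documents. Over 3 to 10 clinics and ICC 0.01 to 0.10, the half-width runs from 1.53 to 2.57 points and coverage of the uncorrected interval from 94.4% down to 74.5%. It is negligible with many clinics and a low ICC, and substantial with few clinics and a moderate ICC. These figures assume equal clinic sizes, SD 6, 62 analysable participants and inference to a wider population of clinics. The plan should make the assumption visible and checkable before recruitment starts.

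**What to change.** 1. Add a coded clinic field and a coded treating-therapist field to Section 2.6.2 and to the clinical data sheet, and carry both into the analysis file.
2. State in Section 2.9 that the 1.5-point half-width holds under independence. Give the expected number of clinics and the half-width over an assumed ICC range, in the manner of the table above.
3. In Section 4.9, add a cluster-aware 95% interval for the primary mean as a sensitivity analysis (a random-intercept model, or a cluster-robust standard error with a small-sample correction). Account for clinic in the exploratory models where the number of clinics allows.

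The cost is two extra fields and a few sentences. The statistical downside is a wider interval with few degrees of freedom if few clinics take part: about 2.65 points for 5 clinics at ICC 0.05. For that reason the cluster-aware interval is proposed as a sensitivity analysis and not as a replacement for the primary one.

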### 2.3. Target Population

The target population will consist of adults receiving conservative physiotherapy for WAD grades I–II or non-surgical post-traumatic neck pain without fracture, instability, or other red-flag conditions. To reduce clinical heterogeneity, the protocol will not include patients requiring surgical management, urgent medical management, or specialised neurological care. Time since injury will be recorded and categorised a priori as early/subacute (up to 3 months), persistent (more than 3 to 6 months), or chronic (more than 6 months), allowing clinical context to be considered in exploratory analyses.

### 2.4. Eligibility Criteria

#### 2.4.1. Inclusion Criteria

Participants must meet the following criteria:Age 18 years or older.Diagnosis of WAD grades I-II or non-surgical post-traumatic neck pain.Referral to physiotherapy or rehabilitation after cervical trauma.Prescription of a home exercise programme as part of usual rehabilitation.Ability to understand the participant information sheet and complete the questionnaire.Written informed consent before data collection.

#### 2.4.2. Exclusion Criteria

Participants will be excluded if they present any of the following:Severe cognitive impairment or inability to complete self-reported questionnaires.Insufficient comprehension of the questionnaire language.Severe neurological deficit requiring urgent medical management.Cervical fracture, instability, infection, tumour, or another red-flag condition requiring medical or surgical management rather than standard outpatient physiotherapy.Refusal or inability to provide informed consent.

### 2.5. Home Exercise Programme Documentation and Standardisation

Because adherence can only be interpreted in relation to a known prescription, all home exercise programmes must be documented before EARS administration. The protocol does not require all patients to receive the same exercises, because programmes are expected to reflect usual individualised care. However, a minimum set of prescription characteristics will be mandatory to ensure reproducibility and allow comparison across participants.

A home exercise programme will be eligible for adherence assessment only if it includes a clearly defined list of exercises, prescribed weekly frequency, estimated session duration, recommended number of sets and repetitions or duration per exercise when applicable, and any progression instructions. The method of patient instruction will also be recorded, including verbal explanation, therapist demonstration, written handout, video material, digital platform, app-based support, or self-monitoring tools. Any sensory or communication adaptations required for older adults or participants with visual or hearing limitations will be documented.

### 2.6. Protocol Variables

#### 2.6.1. Primary Variable

The primary outcome will be adherence to prescribed home exercise, assessed using the total score of the six-item EARS adherence section four weeks after prescription of the home exercise programme [23]. The EARS total score will be analysed as a continuous variable. No validated cut-off for low or high adherence exists for WADs or non-surgical post-traumatic neck pain; therefore, no diagnostic classification based on EARS cut-off values will be used. Any exploratory categorisation, such as tertiles or sample-based percentiles, will be clearly labelled as exploratory and not clinically validated.

#### 2.6.2. Mandatory Core Variables

The following secondary variables will be collected to contextualise adherence:Age and sex.Diagnostic category: WAD grade I-II or non-surgical post-traumatic neck pain.Time since injury and predefined time-since-injury category.Mechanism of injury.Pain intensity using a numerical rating scale or visual analogue scale (VAS).Number of supervised physiotherapy sessions completed before EARS administration.Home exercise programme characteristics: number of exercises, prescribed weekly frequency, estimated session duration, dose, progression instructions, and instructional format.EARS total score and item-level missingness.Self-perceived barriers to exercise.

#### 2.6.3. Optional Contextual Variables

When available, additional contextual variables will be recorded to supplement the primary database, including medication use, relevant comorbidities, and use of digital self-monitoring tools. These variables will not be required for the primary descriptive analysis but may inform exploratory analyses or future protocol refinement.

### 2.7. Exercise Adherence Rating Scale

The EARS will be administered according to the original publication and the selected Spanish-language adaptation [23,28]. The full scale will not be reproduced in the manuscript or Supplementary Material unless permission is obtained from the relevant rights holder. Researchers or clinicians wishing to use the scale should obtain it from the original publication, the published adaptation selected for their setting, or from the developers or rights holder when required. The protocol will use the six-item main adherence section as the primary measure.

